## Abstract

**Background:** It is challenging to maintain effects of public health interventions. For residential health camps benefits often disappear as the child returns home. Furthermore, long-term effects are often not measured or reported. This paper presents the study protocol for an evaluation of an extended maintenance intervention offered to children who have completed a 10-week residential health camp at one of the five Danish Christmas Seal Houses (DCSH). The target group of DSCH is 7–14-year-olds with social, mental, and/or overweight issues and the overall aim of the camp is to increase life satisfaction and a healthy lifestyle. The primary aim of this study is to assess the effectiveness of the maintenance intervention on children's life satisfaction (primary outcome) and BMI *Z*-score (secondary outcome) 1 year after health camp.

**Methods:** The extended maintenance intervention is developed by DCSH and delivered to each child and family individually by an intervention coordinator to help children maintain positive benefits of the health camp on life satisfaction and health behaviors after returning to their homes. Intervention activities target the child and the family. The effect will be tested in a quasi-experimental design: The intervention is offered to half of the children at one of the five DSCH (intervention group, *N*~144) while the other half and the children at the other four DSCH receive a standard maintenance intervention (control group, *N*~894). Children will complete questionnaires on life satisfaction measured by an adapted version of the Cantril ladder and height and weight prior to health camp, at the end of health camp, 3 months and 1 year after the end of health camp. To enable per protocol analysis and nuanced interpretation of effect estimates, we will monitor the implementation of the intervention by a process evaluation study among children, parents, and follow up coordinators using qualitative and quantitative methods.

**Discussion:** We present a systematic approach to evaluating practice-based interventions in a research design. The study will provide new knowledge on the effectiveness of individualized maintenance interventions on long-term effects on life satisfaction and weight loss among children.

**Trial registration:** Prospectively registered at Current Controlled Trials ISRCTN 13011465 https://www.isrctn.com/ISRCTN13011465

## Introduction

Low life satisfaction and overweight are public health concerns among children and adolescents in Denmark as well as in other western countries (1, 2). Overweight and indicators of mental health and subjective well-being (life satisfaction, health-related quality of life) often co-exist i.e., children with overweight often also struggle with physical, mental and social health issues (3, 4), which have a negative impact on their quality of life (5) and with life satisfaction (6). This co-existence has been addressed in several public health interventions. Results on intervention effects on well-being and maintenance of weight loss are limited due to insufficient evidence, however, a review from 2014 found a trend toward effect on quality of life in multidisciplinary interventions (7).

In Denmark, 6–11% of 11–15 year-old children indicate low levels of life satisfaction (8) and 14% of children live with overweight when entering primary schools (9). Both poor life satisfaction and overweight have great impacts on everyday life in childhood and adolescence and are often strong predictors for facing similar problems in adulthood with mental health problems and lifestyle diseases as main consequences (10, 11). Therefore, it is of great importance to apply appropriate interventions which address the broad psychological needs (e.g., low life satisfaction, negative body image, and social isolation), train skills and provide support for behavioral change (12).

A large meta-synthesis found a significant effect of obesity treatment interventions on children and adolescents, however with relatively little clinical relevance, since the changes in BMI *Z*-score (standardized body mass index score for specific populations) were small (13). Another study looked at maintenance of weight loss results after treatment of childhood obesity and found that BMI-*Z* score for the maintenance intervention group remained stable compared to a slight increase in BMI-*Z* score in the control group (14).

To address problems with overweight in 6–11-year-old children, there has been a greater focus on multi-behavioral (diet, physical activity, behavior-changing) interventions in the international literature (15). These interventions have only achieved small, short-term reductions in BMI thus there is a need for long-term follow up and further research to identify maintenance interventions to sustain weight reductions (15). Maintenance interventions are a programmed additional dose of intervention to sustain positive effects of the initial interventions (16). Parental involvement and interventions addressing the home environment may also be effective in reducing overweight among children (17).

Residential programs are sometimes used as an approach to address multiple health behaviors along with mental and social problems in children. Positive short-term effects of these programs on weight loss have been reported whereas reports on long-term effects are limited (18, 19), which is also the case for residential programs in Denmark such as the health camps called the Danish Christmas Seal Houses (DCSH) (20).

Thus, there is a need for developing and testing appropriate forms of maintenance intervention to ensure intervention benefits are sustained over time (14, 15).

For residential health camps, one major challenge for child participants is to maintain a healthy lifestyle when returning to their homes after the end of a stay. At the health camp, the staff and physical surroundings ensure a healthy life style and a focus on well-being, while the home setting often requires a change of behavior for the whole family in order to obtain a healthy lifestyle (21). To support the child in maintaining their weight loss and increased level of life satisfaction, a maintenance intervention should target both the child, the family, and the school and local community. The child must learn to resist unhealthy temptations in the home environment and maintain the positive belief in themselves which has been built op at the camp. Parents need to be role models and make healthy food and emotional support available at home. Schools and communities need to create environments, which promote emotional well-being and make healthy choices the easy choices. A study from 2007 did not find a long-term (1 or 2 years) effect on maintenance of weight loss of either a behavioral skills maintenance intervention or a social facilitation maintenance intervention, compared to a control group in children aged 7–12. However, for both maintenance interventions, a subset of children with low social problems, showed better long-term weight loss maintenance compared with children in the control group (22).

In Denmark, DCSH, offers a 10-week residential stay at one of their five health camps to children and adolescents aged 7–14 with social, mental, and/or overweight problems. The camps have existed in more than 100 years and used to have a special focus on secondary prevention of overweight. In recent years the main purpose of the health camp has been changed and it now aims to increase life satisfaction among participating children, through healthier lifestyle, more physical activity, supporting social relations, and improvement of individual competences such as self-esteem. To maintain the positive changes in the child after moving from the camp- to the family-setting, DSCH has developed two different maintenance interventions. A simple low cost 9-week maintenance intervention which is offered to all children staying at the five health camps (standard maintenance intervention) and a more comprehensive, and thereby resource demanding 16-week maintenance intervention which is offered to half of the children at one of the camps. Both interventions involve the whole family as a target group.

The core of the extended maintenance intervention is an intervention coordinator, who facilitates the transfer of knowledge, competences, and experiences from the camp. The coordinator aims at improving the collaboration among all stakeholders including e.g., parents and teachers in the home, school, and local environment of the child.

The idea is that key people in the child's home environment should help support the child in maintaining the weight loss and better life satisfaction achieved at the camp.

The purpose of this paper is to present the study protocol for the evaluation of the extended maintenance intervention of the DSCH camps compared to the standard maintenance intervention (control group). This includes the process and effect evaluation design, the intervention content, and the procedures for data collection.

The primary objective is to assess the effectiveness of the extended DSCH maintenance intervention at one of the health camps compared to the control group (standard maintenance at all five health camps) on life satisfaction in children 7–14 years old 1 year after the completion of a 10-week health camp (primary outcome). The primary hypothesis is that children receiving the extended maintenance intervention will maintain a higher life satisfaction after participating in the health camp compared to the control group.

The secondary objective is to assess the effectiveness of the extended maintenance intervention compared to the control group on self-reported BMI in children 7–14 years old 1 year after the completion of health camp (secondary outcome). We hypothesize that children receiving the extended maintenance intervention will be more likely to maintain a healthier BMI compared to the control group.

The following research questions form the basis of the evaluation:

Process evaluation:

What are the characteristics of the children and families maintaining their results after 3 months and 1 year despite not receiving the extended maintenance intervention?What are facilitators and barriers in implementation of the extended maintenance intervention in the family and from intervention coordinators?What was the actual dose of intervention in the standard vs. the extended maintenance intervention and the association to the primary and secondary outcomes?

Effect evaluation:

Can an extended maintenance intervention after participating in a residential health camp maintain results on the primary outcome life satisfaction measured on the Cantril ladder and secondary outcome BMI 1 year after the completion of health camp (primary and secondary outcome) or at short-term follow-up (3 months after health camp)?Can an extended maintenance intervention after the residential health camp maintain results on intermediate outcomes: self-efficacy, self-esteem, social relations, health promoting behavior (food, exercise, sleep), school satisfaction, body satisfaction, and parental health promoting behavior, and parental self-efficacy after 3 months and 1 year.

## Methods and Analysis

### Study Setting

#### The Danish Christmas Seal Houses and the Health Camps—A Historical View

In Denmark there is a national focus on childhood overweight and obesity with several initiatives and interventions carried out mainly by volunteers or in municipality settings (23).

Since 1912, DCSH, a private charity foundation in Denmark, has offered sick or vulnerable children a stay at one of their camps. In the early years, focus was on children with tuberculosis, asthma, or other diseases. In the 1960s focus changed to children with overweight and in recent years there has been an increased focus on children with low life satisfaction and social and mental problems. DCSH has thereby adopted the WHO's broad definition of health and includes both physical, social, and mental health in their definition of health among children and adolescents.

DCSH currently runs five health camps in different parts of Denmark. The camps are called Fjordmark, Hobro, Skælskør, Kildemose, and Liljeborg and they offer stays for children from all municipalities in Denmark. The five camps can accommodate between 24 and 48 children at a time with a total of 990 children staying at one of the five camps per year. The children stay at the camp for 10 weeks but return to their homes on the weekends.

The camp accepts children of the age of seven to 14 years (see referral to camp below). Most participating children are between 11 and 14 years old. The distribution of gender is approximately 50/50 with a small overweight of girls. Approximately 5% of the children have a different ethnic background than Danish compared to 11% in the general population. More children attending the health camps have physical or mental problems compared to other children of the same gender and age (24). Compared to other children of the same age, a larger percentage of children attending a health camp live together with parents who have no education or job and/or are divorced or live apart (25). The children struggle with different problems such as low self-esteem, bullying, and/or low life satisfaction. A recent study reveals that 97% of children at the health camps have either overweight or obesity problems (24). Prior to the camp stay, approximately 73% of the children report having a low quality of life (24).

The effectiveness of the camps has been investigated earlier, mostly in smaller studies. In 2008, a study of intervention activities at the Skælskør camp found significant weight reductions by the end of the program compared to baseline (20). An program evaluation of two of the health camps concluded that parents lacked support in order to be able to change their own lifestyle and to support their children in the process of returning home after their stay at camp (26). Historically, DCSH has focused solely on the child and on the time spent at health camp. The earlier vision was to let the children return to their homes with new confidence in themselves, having experienced a remarkable change of lifestyle and self-confidence.

The findings from 2008 were supported by another evaluation of a project which was conducted at two of the camps, Skælskør, and Hobro from 2013 to 2016, with the aim of improving the collaboration between the camps, the families, and home municipalities. The evaluation concluded that the children benefitted greatly from the health camp with higher quality of life, increased belief in themselves, less bullying in their school environment, feeling healthier and losing weight. However, it also highlighted that the children would be expected to benefit more from a more extended collaboration between the health camp and the parents, schools, and municipalities. Due to low response rate with only 5% answering all the questionnaires including the long-term questionnaire 1 year after camp the evaluation had serious limitations especially on the long-term effects 1 year after camp (27).

Based on the recommendations from this evaluation, the two different maintenance interventions included in this study as intervention- and control group have been developed.

#### The Content of the 10-Week Health Camp

The DCSH defines the goal of the health camps as increased life satisfaction among children. According to their program this goal is achieved through healthier diet, more physical exercise, better school performances and a pedagogical philosophy focusing on a strong community at the camps, and support of the development of the children (28). To accomplish these goals, the camps plan a structured and predictable everyday with various planned activities to support the children's self-development. To strengthen children's belief in themselves and to bring their experiences back to their home environment, the camps have a general philosophy and focus on changing the child's narrative e.g., from a ‘child who gets bullied' to ‘child who is good friend'.

When a child is accepted for a stay at one of the camps, the family is invited to an individual pre-visit ~2 months before the stay. During this, they are shown the facilities and are offered the opportunity to address any concerns and uncertainties. The children start at the health camp in groups, and the family is also invited to an information day along with other parents with children in the same group. This information day is scheduled to take place 2–4 weeks before the stay. The families are gathered to meet each other and for the children within the same group to get to know each other.

The 10-week stay at health camps is structured around sleep, meals, and different activities. The children get up and go to bed at specific hours, and in the morning they all go for a short run. Afterwards they go to school on site or attend other activities such as cooking classes, sport activities, talks about different aspect of well-being with reflections on issues like bullying, life satisfaction, how to treat others respectfully etc. After lunch the children have 1.5 h off where they can relax in their bedroom, play board games with others from their group, read, do homework or other quiet activities. In the afternoons and evenings, the children choose from different social activities such as painting, sports activities (e.g., ball games, spinning or fitness) and occasionally watch a movie or play computer games. When the children choose to participate in certain sports activities, they earn points in an internal competition. When a certain amount of points has been collected, they receive a sweatshirt. Often, the staff has organized a common activity for all children in the afternoon or evening.

The children can use their mobile device every day from 5 to 5.30 pm. At all other times it is locked away.

The children are not attending their own schools while at the camp. Instead they go to school at the camp in small groups of 6–12 students. They go to school for 12 lessons per week, which is a lot less than in their own school. They work with a lesson plan from their own schools and are taught Danish, mathematics and a foreign language. The children go to school for 1.5–3 h per day.

Three main meals and two healthy snacks are served at specific times each day and there are specific rules for maximum portion sizes allowed and requirements of eating a minimum amount of vegetables which is individually adjusted for each child. Everybody will at least taste the different components of a meal such as different vegetables. The meals served are healthy meals following the national guidelines for dietary advice in this age group (29). This also means that sugar and fat intake are limited but not prohibited. The philosophy is to give children knowledge about food and exercise by showing them how to cook, eat varied, and discover the fun of new ways to exercise.

#### Referral to Health Camp and Characteristics of Children

Any child and their family can apply for a stay at a DCSH health camp, and it is free of charge since DCSH raises money to run the camps. In the application form, the child, family, or other relevant people describe the rationale for why a stay at a health camp is thought to be a good idea for the child including the concerns and challenges the child faces. The application must be supported by the school and the child's family physician along with a social worker or a psychologist if applicable. The application is sent to DCSH, who distribute the applications to the principal at one of the five camps. The principal assesses the application and considers whether the child would benefit from a stay. Overall, children are accepted unless they do not fulfill the age group specifications, have severe medical symptoms (either psychiatric or physical) or are considered in need of a placement with more support than what can be offered at the camps e.g., for maladjusted children. The camp program is considered a pedagogical offer, not a psychiatric one. If the principal has any uncertainties of whether the child has medical issues, the application is sent to a pediatrician affiliated with DCSH. The pediatrician considers if the applicant could benefit from a stay based on the medical issues. E.g., children are accepted if they are diagnosed with only mild symptoms of a psychiatric disease e.g., ADHD. The principal can also arrange for an early meeting with the child and family to disclose whether the child is believed to benefit from a stay.

#### The Flow of Children at the Health Camps

A group consists of 8–12 children depending on the capacity of each of the different camps, and there are three or four groups at each camp at the same time (Figure 1). The allocation to a group is based mainly on the child's placement on the waiting list which is determined by the reception data of the child's application. Considerations are given to provide balanced gender and age distributions within the groups.

**Figure 1 F1:**
[figure not shown]
Example of the flow of children at the health camps with four groups at the time.

The children do activities both within the groups and together with all participants at the camps. Each group has a team of pedagogues affiliated and each child is allocated a contact pedagogue from the team who takes care of any issues of concerns and communicates with their parents if needed. At the camp there is a continuous overlap between groups. One group completes their 10-week stay on a Friday; the next group starts the following Monday. The two to three other groups at the camp are ~2, 5 and 7 weeks into their stay. After 2–3 weeks, the drill repeats to a total of 10 weeks per group (Figure 1). The argument for doing this is that the health camps have experienced that the children who are already attending the camp can help the new children getting into the DSCH routines etc. Another advantage of this approach is that all children at some time point get the experience of being ‘the old ones' with experience and surplus of mental resources. They can support the new group of children, when they experience homesickness or other challenges from being away from home, which is common.

### Study Design

The effectiveness of the extended maintenance intervention will be evaluated in a quasi-experimental design (30) comparing the intervention group and the control group at long-term follow-up. Parallel to this we will conduct a process evaluation study.

#### Sampling and Allocation to Intervention Groups

Half of the children from the Liljeborg health camp is offered the extended maintenance intervention. The allocation to the intervention group is done by a secretary at the DCSH. The allocation is not random but based on the home municipality of the child (geographical criteria). The Liljeborg health camp covers both municipalities in the Capital Region of Denmark and the Region of Zealand and the distribution is ~50/50 from each region. All 10 municipalities in the Region of Zealand covered by the Liljeborg health camp are allocated to the intervention group. The control group includes children from the Liljeborg health camp along with the four other health camps receiving the standard maintenance intervention (control group 1) and children from the Liljeborg health camp allocated to the standard maintenance intervention (control group 2).

Blinding is not possible in this setting, and the standard maintenance intervention families at Liljeborg will have an idea of the activities going on in the extended maintenance intervention. For the four remaining health camps, families are not aware of any other type of maintenance interventions than the one offered at that specific home, which is the standard maintenance intervention.

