#### Intervention Group: Extended Maintenance Intervention

The extended maintenance intervention is also delivered by an intervention coordinator who is assigned to a family. Some activities are identical to the standard maintenance intervention such as family day and follow up day along with phone calls (Table 1). The extended maintenance intervention encompasses several new initiatives compared to the standard maintenance intervention. It has a duration of ~16 weeks, 6 weeks while the child is at camp and 10 weeks afterwards. The intervention coordinator will participate in home visits and can also participate in different activities such as school visits and network meetings and assist the family in initiating new sports activities or other relevant activities (Table 2). The number of each of the activities are decided in corporation between the family and the intervention coordinator. The intervention has been in constant development since the beginning of 2018 and it is an ongoing process.

**Table 1 T1:** Main similarities and differences between the two maintenance interventions.

**Family collaboration**	**Standard maintenance intervention (control group)**	**Extended maintenance intervention (intervention group)**
Intervention provider	Intervention coordinator	Intervention coordinator
Duration	9 weeks	16 weeks
Intervention concept	Standard	Tailored to each child
Information day before camp	X	X
Family day during camp	X	X
Follow up day 4 weeks after camp	X	X
Phone call/texts to follow up	X	X
Home visits during and after health camp		X
Network meetings		X
School meetings		X
Meeting with health worker or social worker in home municipality		X
Start-up of sports activities		X

**Table 2 T2:** Activities in the extended maintenance intervention and frequency.

**Activities**	**Number**
**Home visits:** The intervention coordinator visits the child's home and talks to the parents and the child, most often separately. The first visit is while the child is still at camp and therefore solely involves a talk with the parents	2–5
**Network meetings:** The intervention coordinator arranges a meeting with relevant participants e.g., parents, schoolteacher, school principal, social and/or health worker from the municipality etc.	0–2
**School meeting:** The intervention coordinator visits the schools along with the child to tell the classmates about the child's experiences at the camp	0–1

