There are four intervention coordinators at the Liljeborg health camp with an educational background as pedagogues. They only get to know the children sparsely during the stay and they get their knowledge through meeting with the pedagogues working at the Liljeborg health camp. The extended maintenance intervention is organized in four settings identified in the program theory (see below), which are thought to influence how well a child adjusts to coming home after a stay at Liljeborg health camp and maintain his or her goals:

*1: The home setting:* The intervention coordinator visits the family and helps them with any concerns e.g., how to incorporate healthy habits in their everyday life, how to help their child with educational and social concerns at school e.g., friends and bullying. The intervention coordinator may take on many roles, but the main task is to help the family to a better understanding of their child's challenges and in many ways act as a discussion partner and present different tools to overcome challenges.

*2: The school setting*: The intervention coordinator sometimes helps the child in preparing a presentation for his or her school class about the time at the health camp and the developing journey, they have been through. The intervention coordinator sometimes also has a continuous dialogue with the schoolteachers to support the child, most often by email or phone.

Another activity is network meetings. During a network meeting, the family and the intervention coordinator meet with relevant professionals e.g., schoolteachers, principal at the home school, or caseworkers from the health or social department at the municipality to collaborate about the best ways to help the child. In some cases, a follow up meeting is arranged about 1 month later to pick up any challenges which have been faced in the period.

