**Figure 4 F4:**
[figure not shown]
Flowchart of expected numbers of participants.

Historically it has been difficult to reach a satisfactory response rate for the long-term follow up questionnaires as mentioned before (27).

We used already collected questionnaire data from the camps to calculate the number of children needed to detect changes on the primary outcome (see Table 3). We made a random retrieval of 50 children from each of the five health camps, a total of 250.

Based on this calculation, we found a SD of 2.1. A prospective power calculation shows that with 80% power, we will be able detect a difference of 0.53 points on the Cantril ladder between groups with 144 in the intervention group and 894 in the control group. These power calculations are based on the assumptions that all the children complete the stay at the camp and all the children allocated to the extended maintenance intervention at the Liljeborg health camp, will accept this. If we assume there is a 8% drop out of all health camps, the calculation with 132 in the intervention group and 822 in the control group, we will be able to detect a difference of 0.55 on the Cantril ladder, making it a very small difference.

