### Data Analysis

We will use descriptive statistics to investigate baseline equivalence and loss to follow up. We will graphically visualize the development over time in both intervention group and control group 1 for the primary and secondary outcomes.

We will analyze the effectiveness of the extended maintenance intervention compared to control group 1 on the primary and secondary outcomes, using linear regression analysis and on explorative outcomes using logistic regression analyses. We will apply an intention-to-treat approach including all children in the intervention group they initially have been allocated to irrespective of whether they have completed the intervention or are lost to follow-up. Missing data will be replaced by multiple imputation. We will perform complete case analysis for sensitivity analyses.

The effect analyses will be adjusted for baseline factors including gender and age of the child, life satisfaction, BMI-*Z* score, and parental socioeconomic position.

For the total population at all five camps, we will calculate the standard deviation of the primary and secondary outcomes right after camp to calculate Cohen's *d* effect size.

Furthermore, we will perform sensitivity analysis restricted to the data from the Liljeborg health camp to identify any differences between camps (control group 2). We will investigate the association between intervention dose and effect (per protocol analyzes).

We will investigate if the effect differs by subgroups (see moderators in Figure 2).

We will summarize process measures using appropriate descriptive statistics including proportions, means (SD), and medians (IQR).

We will identify who is in most need of the intervention and find out who does not need the intervention.

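### The extended intervention is assigned by municipality (10 form the whole intervention arm), but the detectable difference and the stated linear regression make no allowance for clustering by municipality.

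*Protocol article*

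**What the plan says.** Sampling and Allocation to Intervention Groups gives the rule: "The allocation is not random but based on the home municipality of the child (geographical criteria". It then fixes the units: "All 10 municipalities in the Region of Zealand covered by the Liljeborg health camp are allocated to the intervention group". The other Liljeborg children, and all children at the other four camps, receive standard maintenance.

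Sample Size Calculations takes an SD of 2.1 from existing questionnaire data. For 80% power and 894 controls it concludes: "we will be able detect a difference of 0.53 points on the Cantril ladder between groups with 144 in the intervention group". With 8% not completing camp (132 and 822), the figure becomes 0.55, which the article calls very small. The assumptions it lists are that every child completes the stay and that every allocated child accepts the extended offer. Clustering is not among them.

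Data Analysis specifies the effect analyses, "using linear regression analysis and on explorative outcomes using logistic regression analyses". The covariates are gender, age, baseline life satisfaction, baseline BMI Z-score and parental socioeconomic position. No cluster term or cluster-robust variance is named. A sensitivity analysis is restricted to Liljeborg, where allocation is still by municipality.

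**The concern.** When whole municipalities are assigned, children from one municipality always fall in the same arm at Liljeborg. Anything they share then adds to the variance of the arm contrast and does not cancel. Such sharing is plausible here, because the extended intervention is organised around the school, municipal services and local leisure clubs. Ordinary regression counts about 144 independent intervention children, while the assignment supplies 10 units.

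The result would be confidence intervals that are too narrow and p-values that are too small for life satisfaction and BMI, and a stated detectable difference with no design effect. The article's ethics section says the evaluation will have implications for the future of the extended intervention, so a false-positive primary result would have practical consequences.

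**Working it through.** **Inputs from the article:** SD 2.1; power 80%; 144 v 894 children, and 132 v 822 after 8% dropout; 10 intervention municipalities.

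**Assumptions:** two-sided alpha of 0.05 (not stated); equal cluster sizes, m = 144/10 = 14.4; ICC 0.01 to 0.05 (none is given).

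**Step 1: reproduce the stated figures.** For independent children:

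MDD = (1.9600 + 0.8416) × SD × √(1/n₁ + 1/n₂)

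- 144 v 894: 2.8016 × 2.1 × √(0.006944 + 0.001119) = 0.528 (stated 0.53).
- 132 v 822: 2.8016 × 2.1 × √(0.007576 + 0.001217) = 0.552 (stated 0.55).

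A one-sided 5% test would give 0.47 and 0.49. The arithmetic is right, and the design effect used is 1.

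**Step 2: add municipality clustering.**

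- Design effect DE = 1 + (m − 1) × ICC = 1 + 13.4 × ICC.
- Both arms clustered alike: MDD = 0.528 × √DE.
- Intervention arm only: MDD = 2.8016 × 2.1 × √(DE/144 + 1/894).
- Power at 0.53 (both arms) = Φ(0.53/SE − 1.96), with SE = 2.1 × √DE × √(1/144 + 1/894).
- True type I error of the unclustered test (both arms) = 2Φ(−1.96/√DE).

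| Assumed ICC | DE | SE ratio | MDD, both arms | MDD, intervention arm only | Power at 0.53 | True error of nominal 5% test |
|---|---|---|---|---|---|---|
| 0.01 | 1.134 | 1.065 | 0.56 | 0.56 | 75% | 6.6% |
| 0.02 | 1.268 | 1.126 | 0.60 | 0.59 | 70% | 8.2% |
| 0.05 | 1.670 | 1.292 | 0.68 | 0.66 | 59% | 12.9% |

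The intervention-arm-only column is shown because the article does not give the number of control municipalities. These are normal approximations and ignore the lost degrees of freedom with only 10 intervention clusters.

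**Step 3: allow for baseline adjustment.** The stated 0.53 is unadjusted, but the planned model includes baseline life satisfaction. With an assumed baseline to 1-year correlation of 0.5, and the ICC unchanged by adjustment:

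- No clustering: 0.528 × √(1 − 0.25) = 0.46.
- ICC 0.02: 0.458 × 1.126 = 0.52.
- ICC 0.05: 0.458 × 1.292 = 0.59.

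Break-even with 0.528 is at DE = 1/0.75 = 1.333, which is ICC = 0.333/13.4, or about 0.025.

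**The case against.** **A condensed article may leave variance estimation to an analysis plan that is not shown, and linear regression does not exclude robust errors.** This has some force for the analysis. However, the article names the model and the covariates and reports a finished power calculation. Robust errors added later would leave 0.53 and 0.55 as independence figures.

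**Every size rests on an assumed ICC.** This stands. Adjustment for socioeconomic position could also shrink the ICC, and at 0.01 the change is modest. The direction holds for any positive ICC.

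**A reader might infer that the planned analysis cannot detect 0.53.** The documents do not support that. Step 3 shows that adjustment can offset a small ICC in the detectable difference. It does not make an unclustered standard error valid.

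**A reader might also add intake groups as a clustering level.** The article says "A group consists of 8–12 children depending on the capacity of each of the different camps", but places are filled mainly by waiting-list position, with attention to gender and age. About half of Liljeborg's children are in each arm, so its groups probably mix the arms and a shared group effect largely cancels. A full design effect for intake group is not justified.

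**A reader might make coordinators the main problem.** "There are four intervention coordinators at the Liljeborg health camp with an educational background as pedagogues", and "The extended maintenance intervention is also delivered by an intervention coordinator who is assigned to a family". With even caseloads (144/4 = 36), an ICC of 0.01 to 0.05 and clustering in the intervention arm only, DE is 1.35 to 2.75, the detectable difference 0.60 to 0.84 and the type I error 8.6% to 21.6%. This is only an upper-end scenario. Even caseloads are assumed, standard maintenance is also delivered by coordinators, and the Liljeborg coordinators keep activity logs for children in both arms, so part of any provider effect may cancel.

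**Conclusion.** The point holds for municipality. Assignment is by municipality, 10 municipalities make up the intervention arm, the stated detectable differences reproduce under independence, and the stated model has no allowance for clustering. Under an assumed ICC of 0.01 to 0.05, the true standard error is about 6% to 29% larger than the one the model would report, and a nominal 5% test runs at about 6.6% to 12.9%. The unadjusted detectable difference is about 0.56 to 0.68 (0.56 to 0.66 if only the intervention arm is clustered). Whether the baseline-adjusted analysis does worse than 0.53 depends on an ICC and a baseline correlation that the article does not give. That the standard errors are too small requires only a positive within-municipality correlation. Correcting them does not remove confounding by region or camp, which is a separate matter.

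**What to change.** - Analyse the primary and secondary outcomes with a linear mixed model with a random intercept for home municipality, or with municipality-clustered robust errors. In either case use a small-sample correction (Kenward-Roger or CR2), because the intervention arm has only 10 clusters.
- Carry municipality into the multiple-imputation model.
- Add a sensitivity analysis for clustering by coordinator.
- Restate the detectable difference over a stated ICC range, with the alpha level, and say whether it is adjusted for baseline. Report the estimated ICC with the results.

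The cost is in wording and analysis, with no change to the design. Municipality is the allocation key, so the camp organisation holds it, and coordinators complete questionnaires for each intervention family. The article does not say that municipality is in the research dataset, so this should be confirmed. The downside is somewhat wider intervals and a less favourable stated figure.
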